## Abstract

**Background:**

Hyperemesis gravidarum (HG), or intractable vomiting during pregnancy, is the single most frequent cause of hospital admission in early pregnancy. HG has a major impact on maternal quality of life and has repeatedly been associated with poor pregnancy outcome such as low birth weight. Currently, women with HG are admitted to hospital for intravenous fluid replacement, without receiving specific nutritional attention. Nasogastric tube feeding is sometimes used as last resort treatment. At present no randomised trials on dietary or rehydration interventions have been performed. Small observational studies indicate that enteral tube feeding may have the ability to effectively treat dehydration and malnutrition and alleviate nausea and vomiting symptoms. We aim to evaluate the effectiveness of early enteral tube feeding in addition to standard care on nausea and vomiting symptoms and pregnancy outcomes in HG patients.

**Methods/Design:**

The MOTHER trial is a multicentre open label randomised controlled trial (www.studies-obsgyn.nl/mother). Women ≥ 18 years hospitalised for HG between 5 + 0 and 19 + 6 weeks gestation are eligible for participation. After informed consent participants are randomly allocated to standard care with intravenous rehydration or early enteral tube feeding in addition to standard care. All women keep a weekly diary to record symptoms and dietary intake until 20 weeks gestation. The primary outcome will be neonatal birth weight. Secondary outcomes will be the 24-h Pregnancy Unique Quantification of Emesis and nausea score (PUQE-24), maternal weight gain, dietary intake, duration of hospital stay, number of readmissions, quality of life and side-effects. Also gestational age at birth, placental weight, umbilical cord plasma lipid concentration and neonatal morbidity will be evaluated. Analysis will be according to the intention to treat principle.

**Discussion:**

With this trial we aim to clarify whether early enteral tube feeding is more effective in treating HG than intravenous rehydration alone and improves pregnancy outcome.

**Trial registration:**

Trial registration number: NTR4197. Date of registration: October 2^nd^ 2013.

**Electronic supplementary material:**

The online version of this article (doi:10.1186/s12884-016-0815-1) contains supplementary material, which is available to authorized users.

## Background

Nausea and vomiting in pregnancy (NVP) is common, affecting 50–80 % of pregnancies [1]. Often these symptoms are mild and self-limiting and resolve without intervention in the second trimester. In other cases however, severe intractable vomiting can lead to dehydration, electrolyte disturbances and significant weight loss necessitating hospital admission. The condition of intractable vomiting during pregnancy is called hyperemesis gravidarum (HG) [2]. HG has repeatedly been associated with poor pregnancy outcome including low birth weight (LBW, <2500 g: OR 1.42), small for gestational age (OR 1.28) and prematurity (OR 1.32) [2–4]. Furthermore, HG has a major impact on maternal wellbeing and quality of life [5–7] and remains the largest single cause of hospital admission in early pregnancy [8, 9]. However, the aetiology of HG is poorly understood [10–12].

Approximately 0.8–2 % of all pregnancies are complicated by HG [2]. Currently, there are no treatments with proven efficacy available according to the latest Cochrane review on interventions for nausea and vomiting in early pregnancy [1]. Hospitalisation can be required for intravenous treatment of dehydration and electrolyte imbalance. Currently, women who suffer from HG do not receive any particular nutritional attention, although enteral tube feeding is sometimes used as a treatment of last resort [2, 13]. Enteral tube feeding effectively treats both dehydration and malnutrition in non-pregnant patients with poor intake [14] and has been shown to be safer than parenteral nutrition in pregnancy [15]. Moreover, in several small studies in women with HG, which did not employ a control group, it alleviated symptoms and was well tolerated if continued in a home setting [16–18]. There have been no controlled trials to investigate the extent to which enteral tube feeding can positively affect pregnancy outcome and maternal quality of life, nausea and vomiting symptoms or time in hospital.

At present, there is no evidence on the effectiveness and efficiency of rehydration and dietary interventions for HG. We hypothesise that enteral tube feeding in addition to standard care is a more effective treatment for HG symptoms than standard care with intravenous rehydration alone, and improves pregnancy outcome.

This multicentre randomised controlled trial (RCT) aims to compare early enteral tube feeding in addition to standard care, with standard care alone. Outcomes of interest are birth weight and maternal nausea and vomiting symptoms, maternal quality of life, duration of hospitalisation, weight gain and neonatal morbidity. The study is conducted within the Dutch Consortium for Studies in Obstetrics, Fertility and Gynaecology (www.studies-obsgyn.nl).

## Methods/Design

### Participants/ eligibility criteria

Patients ≥ 18 years of age are eligible if they have been admitted to hospital because of HG (first admission or readmission) at a gestational age between 5 + 0 and 19 + 6 weeks. Patients with singleton or multiple pregnancies are eligible. A diagnosis of HG is made if excessive nausea or vomiting necessitates hospital admission, in the absence of any other obvious cause such as drug induced vomiting or infection.

Exclusion criteria are mola hydatidosa pregnancy, non-vital pregnancy, acute infection causing vomiting (e.g. appendicitis, pyelonephritis), contraindication for enteral tube feeding (e.g. oesophageal varices, allergies to enteral tube mix compounds) or HIV infection.

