**Fig. 1 Fig1:**
[figure not shown]
CONSORT 2010 flow diagram MOTHER trial

Randomisation is performed by a web based computerised program using permuted-block randomisation. Randomisation is allocated in a 1:1 ratio for standard care or enteral tube feeding in addition to standard care, with a block size of four. Stratification according to centre is applied.

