## Outcome measures

### Primary outcome measure

The primary outcome will be neonatal birth weight.

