## Statistical issues

### Sample size

The sample size is based on a difference in mean birth weight of 200 g (SD 400 g) between the intervention group and the control group, which we consider clinically relevant. With a beta of 0.2 and alpha of 0.05 and a possible 10 % loss to follow up, we need to randomise 120 participants (60 per arm). This sample size is also large enough to detect a two point reduction in PUQE-24 score 1 week after randomisation (maximum 15 points, SD 3 points) and differences in quality of life, psychopathology and general health questionnaires ≥ 10 %.

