### Data analysis

Data will be analysed according to the intention to treat principle. Difference in birth weight will be assessed using parametric testing. PUQE-24 score will be analysed using multivariate regression and repeated measurements ANOVA or mixed models, as will be quality of life assessments. Other secondary outcomes will be addressed in a similar manner. For non-normally distributed variables non-parametric equivalents will be used. To evaluate the potential of each of the strategies, we will also perform a per protocol analysis, taking into account only those women that were treated according to protocol.

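### Multiple pregnancies are eligible, but the primary birth-weight comparison fixes neither the unit of analysis nor any allowance for plurality; a mother-level, plurality-adjusted analysis would be better on either reading

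*Protocol article*

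**What the plan says.** Under Participants/eligibility criteria, the protocol article admits both kinds of pregnancy: "Patients with singleton or multiple pregnancies are eligible". Women are randomised: "Randomisation is allocated in a 1:1 ratio", in blocks of four, with centre as the only stratification factor.

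Under Primary outcome measure: "The primary outcome will be neonatal birth weight". Under Data analysis, the whole description of the primary comparison is that "Difference in birth weight will be assessed using parametric testing", within an intention-to-treat analysis. The same paragraph names regression and mixed models for the PUQE-24 score and quality of life, but not for birth weight.

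Under Sample size: "The sample size is based on a difference in mean birth weight of 200 g (SD 400 g"), and "we need to randomise 120 participants (60 per arm"). The calculation uses a single SD and counts women. The article does not say whether that SD describes singletons or a mixed population, and it gives no expected share of multiples.

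**The concern.** A woman with twins contributes one randomisation but two birth weights. The two infants share a mother and an allocation, so their weights are correlated, and both are much lighter than a typical singleton. Two problems can follow.

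1. **Counting siblings as independent.** If each infant enters a two-group test as a separate observation, the standard error is too small and the test rejects too often.
2. **Leaving the plurality gap in the error term.** Even with one value per mother, an unadjusted comparison puts the singleton-multiple difference into the residual variance. Multiples are not a stratification factor, so chance imbalance between arms goes uncorrected.

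The numbers involved are small. With 108 evaluable women, a 2% twin share means about 2 twin pregnancies (0.02 × 108 = 2.2) and an 8% share about 9 (0.08 × 108 = 8.6). A split of 3 against 1 is therefore quite possible. The trial is open label, so leaving several defensible treatments of twins open (all infants, sibling mean, first-born, singletons only) also leaves room for a choice made after the data are seen.

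**Working it through.** **Inputs from the article:** difference 200 g, SD 400 g, alpha 0.05, power 0.80, 10% loss, 60 women per arm.

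**Assumptions not in the article:** twin share p of 2-8% of pregnancies; twins lighter by g = 700-900 g; within-pair correlation r = 0.5; 400 g is the SD within plurality; two-sided test.

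**Step 1: the plan's own figure.** n per arm = 2 × (1.960 + 0.842)² × (400/200)² = 62.8, so 63. Allowing for 10% loss, 63/0.9 = 70 per arm, or 140 women, not 120. With 60 randomised and 10% lost, 54 per arm are evaluable, and power is 0.74 by the normal formula (0.73 by t) before any twins. The gap between 120 and 140 is a separate matter. It is used here only to set the baseline.

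**Step 2: one value per mother, unadjusted.** Variance = (1−p)·400² + p·400²·(1+r)/2 + p(1−p)·g².

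- p = 2%, g = 700: 156,800 + 2,400 + 9,604 = 168,804, SD 411 g. Power = Φ(200/(411·√(2/54)) − 1.96) = 0.72.
- p = 8%, g = 900: 147,200 + 9,600 + 59,616 = 216,416, SD 465 g. Power = 0.61.

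The type I error is not affected, because the women are independent.

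**Step 3: infants analysed individually, pairing ignored.** Let f = 2p/(1+p) be the share of infants who are twins. Per mother randomised, the variance of an arm mean is:

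- assumed by the test: [400² + f(1−f)g²]/(1+p)
- actual: [(1−p)(400² + f²g²) + p(4(1−f)²g² + 2·400²(1+r))]/(1+p)²

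For p = 5%, g = 900: f = 0.0952, assumed 218,853, actual 286,251, ratio 1.308. The standard error is understated by a factor of √1.308 = 1.144, so type I error = 2·[1 − Φ(1.96/1.144)] = 0.087. The same formula gives 0.064 for p = 2%, g = 700 and 0.095 for p = 8%, g = 900.

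**Step 4: simulation**, 54 mothers per arm, r = 0.5, 6,000 replicates per setting:

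| Twin share, gap | Infant-level t test: type I / power | One value per mother, unadjusted: power | One value per mother, adjusted for plurality: type I / power |
|---|---|---|---|
| 2%, 700 g | 0.058 / 0.68 | 0.71 | 0.050 / 0.74 |
| 3%, 800 g | 0.076 / 0.66 | 0.70 | 0.048 / 0.73 |
| 5%, 900 g | 0.083 / 0.59 | 0.64 | 0.047 / 0.73 |
| 8%, 900 g | 0.099 / 0.55 | 0.60 | 0.053 / 0.75 |

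The type I error of the unadjusted mother-level test was 0.050-0.052. The closed forms in steps 2 and 3 agree with the table within simulation noise. A wider grid (r = 0.7, twin share 2-10%, gap 600-1000 g) gave infant-level type I error of 0.059-0.107.

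**Step 5: one extra twin pair in an arm of 54.** At infant level the arm mean moves by 2g/55, or 25-33 g. With one value per mother it moves by g/54, or 13-17 g. Against the 200 g target this is roughly 13-16% and 6-8%.

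**The case against.** A reader might infer that the plan treats infants as independent and that its type I error is therefore inflated. The article does not say so. The sample size counts women, which fits one value per pregnancy at least as well, and the term parametric testing also covers regression and mixed models. The inflation in step 3 belongs to one possible reading.

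A reader might also infer that 400 g excludes multiples. No source is given for the SD, so this cannot be shown. If 400 g already describes a mixed population, the power loss in step 2 has in part been allowed for. Nor does the article establish that plurality is recorded: Data collection lists birth outcomes and obstetric history but does not name plurality, and the case report form is not shown.

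The article is also a condensed account. The full protocol is said to be available separately and may settle how siblings are handled. At a 2% twin share the mother-level loss is only 2 to 3 percentage points, and much of the shortfall from 0.80 comes from the planned size rather than from twins.

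All of this stands, and it limits the claim. It does not remove the point, which is not that detail is missing. The article fixes the eligibility, the endpoint and a plain two-group comparison, and for that combination a better method exists whichever unit is meant.

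**Conclusion.** The point holds as a should-fix improvement to the primary analysis. The plan admits multiples without fixing how they enter a birth-weight comparison.

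- If infants are tested individually with no allowance for pairing, type I error is about 6-10% instead of 5%.
- If one unadjusted value per mother is used, type I error is sound, but power drops from about 0.73 to 0.71-0.60, provided that 400 g is the within-plurality SD.
- A mother-level analysis adjusted for plurality has type I error near 5% and power of about 0.73-0.75 in the same settings.

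The direction is firm. The size rests on assumed twin shares of 2-8%, gaps of 700-900 g and a pair correlation of 0.5, none of which the article gives. At the low end the effect is minor.

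**What to change.** - **Primary analysis:** make the mother the unit. Use linear regression of one birth weight per pregnancy (the sibling mean for multiples) on allocation, with plurality (single or multiple) as a covariate. An infant-level mixed model or GEE clustered on the mother, with the same covariate, is an acceptable alternative.
- **Covariate definition:** take plurality as known at or before randomisation, from early ultrasound. Entry starts at 5+0 weeks, so the number of infants at birth can differ from the number at entry and would be a post-randomisation variable.
- **Neonatal secondary outcomes:** cluster SGA, hypoglycaemia, hyperbilirubinaemia and congenital anomalies on the mother.
- **Sensitivity analysis:** repeat the primary comparison in singleton pregnancies only.
- **Sample size:** state which population the SD of 400 g describes.

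The cost is one degree of freedom, some wording in the analysis section, and a check that plurality at randomisation is recorded. No additional participants are needed for this change.

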### Procedures, recruitment and randomisation

This study is a nationwide multicentre open label RCT conducted within the Dutch Consortium for Studies in Obstetrics, Fertility and Gynaecology, a nationwide collaboration of hospitals in the Netherlands. The staff and/or local research coordinator of the participating hospitals identifies eligible women. After counselling and reading the patient information form, patients are asked for written informed consent. Patient information is provided in Dutch and English. See Fig. 1.

**Fig. 1 Fig1:**
[figure not shown]
CONSORT 2010 flow diagram MOTHER trial

Randomisation is performed by a web based computerised program using permuted-block randomisation. Randomisation is allocated in a 1:1 ratio for standard care or enteral tube feeding in addition to standard care, with a block size of four. Stratification according to centre is applied.

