### Intervention

Participants are allocated to standard care or enteral tube feeding in addition to standard care. Standard care consists of intravenous rehydration and, when considered necessary, laboratory monitoring, electrolyte and/or vitamin supplementation, antiemetic medication and dietetic advice. Type of rehydration regimen, medication and duration of hospitalisation is prescribed according to local protocol. In case of prolonged hospital admission or readmissions, tube feeding can be initiated at the decision of the attending physician.

When allocated to the intervention group, participants receive a nasogastric tube as soon as possible after randomisation, in addition to standard care. If the initial nasogastric tube is dislocated or poorly tolerated a nasoduodenal or nasojejunal insertion can also be considered. Tube feeding regimen and mix is prescribed according to local protocol. As soon as tube feeding is tolerated and participants have received safety instructions (e.g. recognising symptoms that need to be evaluated in hospital, because of potential tube blockage, dislocation or aspiration), discharge home with tube feeding is encouraged under the guidance of a hospital dietician. Energy intake per tube is continued at least until the patient is able to maintain an oral intake of 1000 cal per day for one week. According to the NICE guideline on nutrition, tube feeding in a home setting is considered to be safe [14].

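### A single fixed block size of four within each centre of this open-label trial could let staff foresee up to one allocation in three with certainty

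*Protocol article*

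**What the plan says.** All of this is in the Methods/Design section of the protocol article.

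- Under Procedures, recruitment and randomisation, in the paragraph after Fig. 1: "Randomisation is performed by a web based computerised program using permuted-block randomisation". The ratio is 1:1, "with a block size of four", and "Stratification according to centre is applied". One size is given, with no mention of varying it or withholding it from sites.
- At the start of the same section: "This study is a nationwide multicentre open label RCT". On who recruits: "The staff and/or local research coordinator of the participating hospitals identifies eligible women".
- Under Intervention, the allocation is visible at the bedside. In the tube-feeding arm, "participants receive a nasogastric tube as soon as possible after randomisation".
- Under Participants/eligibility criteria: "A diagnosis of HG is made if excessive nausea or vomiting necessitates hospital admission", once other obvious causes are ruled out. First admissions and readmissions both qualify, from 5+0 to 19+6 weeks. No symptom score is required.
- Under Sample size, 120 women are planned (60 per arm). The number of centres and the recruitment per centre are not stated.

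**The concern.** A web-based program hides the list, but it cannot hide what follows from allocations already seen. In a 1:1 block of four, the last arm is fixed by the first three, and the third is fixed whenever the first two agree. Stratifying by centre gives each hospital its own sequence, so the staff who need to count are the staff who saw the earlier allocations.

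This trial leaves some room to act on that knowledge. Entry rests on a clinical judgement that admission is needed, and a woman passed over at one admission can be approached at a readmission. Clinicians may also hold views on who needs a tube. The Background says tube feeding is already used when other options have failed, and the Intervention section lets the physician start it in the control arm.

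If more severely ill women were steered towards or away from one arm, severity would be confounded with treatment for both birth weight and PUQE-24. That birth weight is measured objectively gives no protection, because the selection takes place before randomisation.

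**Working it through.** The article states no predictability figure, so there is none to reproduce. The inputs are block size 4, ratio 1:1, strata = centres and total 120, all from the sections cited above.

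**Complete blocks.** There are six equally likely sequences of two and two.

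- Probability that the next arm is certain, by position: 0, 0, 1/3 (first two agree in 2 of 6 sequences), 1.
- Share certain = (0 + 0 + 1/3 + 1)/4 = 8/24 = 33.3%. In 120 women that is 40.
- Probability of a correct guess, always naming the arm with more places left: 1/2, 2/3, 2/3, 1. The average is 17/24 = 70.8%.

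**Incomplete last blocks.** The same position probabilities are summed over k women per centre. The values of k are assumptions.

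| Women per centre | Certain per centre | Share certain | Best guess correct | Certain among 120 |
|---|---|---|---|---|
| 3 | 1/3 | 11.1% | (11/6)/3 = 61.1% | 40 centres × 1/3 = 13.3 |
| 6 | 4/3 | 22.2% | 4/6 = 66.7% | 20 centres × 4/3 = 26.7 |
| 10 | 8/3 | 26.7% | (41/6)/10 = 68.3% | 12 centres × 8/3 = 32 |
| any multiple of 4 | k/3 | 33.3% | 70.8% | 40 |

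With one or two women at a centre, nothing is certain.

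**Alternatives.** Fixed sizes were enumerated. Random sizes were simulated with 4,000 sequences each of 12 and of 24 women, for an observer who knows the set of sizes but not the size of each block.

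| Scheme | Certain | Best guess correct |
|---|---|---|
| Fixed 4 | 33.3% | 70.8% |
| Fixed 6 | 25.0% | 68.3% |
| Fixed 8 | 20.0% | 66.6% |
| Random 4/6 | 5.7-6.3% | 67.9-68.7% |
| Random 2/4/6 | 3.4-3.7% | 69.3-69.8% |
| Random 4/6/8 | 2.3-2.4% | 66.5-67.4% |

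A larger fixed block helps little. Varying the size removes most of the certainty but leaves the guess rate almost unchanged.

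**Which check would detect steering.** Suppose that at every certain slot women bound for one arm are 0.5 SD sicker than average and women bound for the other are 0.5 SD less sick.

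- Each block position goes to each arm half the time, so the mean at position 4 is 1/2 × 0.5 + 1/2 × (−0.5) = 0. Position 3 gives 0 by the same symmetry. A comparison by position shows nothing.
- Between arms, the difference is 0.5 − (−0.5) = 1.0 SD in certain slots and 1/3 × 1.0 = 0.33 SD overall.

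The comparison therefore has to be between arms, split by whether the slot was predictable.

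**Precision of that check.** At the ceiling of 40 predictable slots there are about 20 per arm. Assume that the PUQE-24 SD of 3 points in the Sample size section also holds at baseline. The standard error is then 3 × √(1/20 + 1/20) = 0.95, and the 95% interval is about ±1.96 × 0.95 = ±1.9 points.

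**The case against.** The strongest reply is that one in three is a ceiling. It needs complete blocks, staff who know or infer the size, and someone who follows every allocation at the centre. The article establishes none of these, and 120 women spread over a nationwide network may mean few per centre. This stands, and it is why the figure is given as an upper bound with a range.

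A reader might infer from the published block size that recruiting staff knew it. The documents do not show this. The trial was registered in October 2013, the article's DOI carries 2016, recruitment status is not stated, and the full protocol is not at hand.

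A reader might also infer that concealment has failed, or that the results are biased. Neither is supported. Even at the ceiling, two thirds of allocations are not certain, and nothing shows that anyone acted on a prediction. Entry is also not wholly open-ended, because the woman must already be in hospital for this condition.

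Nor is it right that nothing could be done in analysis. PUQE-24, HIS and NVPQoL are recorded on the day of randomisation, so measured severity can be examined and adjusted for. Selection on what is not measured cannot.

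Finally, varying block sizes barely changes the best-guess rate. That is true. The gain lies in removing certainty, which is the clearest opening for deliberate steering.

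**Conclusion.** The point holds as an avoidable risk. The article itself fixes one small block size within centre in an open trial with visible allocation and local recruitment, so this is a stated choice and not a detail left to another document. For staff who know or infer the size and track allocations, up to 33.3% of allocations (40 of 120) are foreseeable with complete blocks, and about 11% to 27% at 3 to 10 women per centre. The enumeration is exact. How far it applies depends on recruitment per centre and on staff knowledge, and the article gives neither. The change is worth making, but nothing here shows that selection bias took place.

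**What to change.** **For any women still to be randomised:** set the web program to randomly varying block sizes within centre, for example 4, 6 and 8, or 2, 4 and 6. Do not disclose the sizes to sites. Certain allocations fall to about 2-4%. This takes a program setting and a short amendment. The price is a slightly larger possible imbalance within a centre: at most half the block, so up to 4 with a block of eight against 2 with a block of four.

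**For women already randomised in blocks of four:** classify each slot from the randomisation log. A slot was predictable if it was fourth in its block, or third after two identical allocations. Compare baseline PUQE-24 and gestational age between arms, separately for predictable and unpredictable slots. Do not compare by block position alone, because opposite shifts in the two arms would cancel. This uses data already collected and can be done even if recruitment has ended. A clean result would be reassuring but not conclusive: precision is limited, only measured severity is covered, and the article does not say whether the questionnaire on the day of randomisation comes before the allocation is known.
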